## Methods and analysis

2

### Study design

2.1

This study employs a prospective, longitudinal, single-blind RCT design with three primary assessment timepoints (T0, T1, T2) and a long-term follow-up assessment (T3), and experimental psychological intervention with random allocation of participants across three groups (Figure 1): (A) Control group (G1): Treatment as usual (TAU) receiving standard psychological support; (B) Active control group (G2): TAU plus psychoeducational intervention; (C) Experimental group (G3): TAU plus EMDR R-TEP protocol.

**Figure 1 fig1:**
[figure not shown]
Flowchart.

The study follows a monocentric organizational structure, conducted within a single Breast Unit affiliated with ASST Rhodense. This investigation pursues non-commercial (non-profit) aims, solely for scientific and clinical purposes. The study protocol conforms to Consolidated Standards of Reporting Trials (CONSORT) guidelines (Schulz et al., 2010).

### Participants

2.2

#### Recruitment and setting

2.2.1

Breast cancer patients will be recruited continuously from the Breast Unit of the Oncology Department at ASST Rhodense (Milan, Italy). Recruitment is integrated within the standard clinical pathway of the Breast Unit. During routine outpatient consultations, medical staff will identify potentially eligible patients, conduct a preliminary screening of medical inclusion/exclusion criteria (e.g., absence of metastatic disease), and refer suitable candidates to the clinical psychology service. Clinical psychologists/psychotherapists will then conduct a psychological screening to verify remaining eligibility criteria (e.g., absence of severe psychiatric conditions, cognitive capacity to provide informed consent), provide information about study objectives and procedures, and obtain written informed consent. Patients will be informed of their right to withdraw at any time without consequences for their clinical care. The recruitment period is estimated at approximately 6 months.

#### Inclusion criteria

2.2.2

Participants will be eligible if they: (1) are biologically female; (2) are aged between 18 and 80 years; (3) Have received first diagnosis of breast cancer; (4) Have scheduled surgical intervention (mastectomy or quadrantectomy); (5) Demonstrate excellent comprehension of Italian language; (6) Provide voluntary consent to participate in the study.

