### Psychological trauma and oncological illness

1.1

Literature suggests that cancer diagnosis and surgical treatment can trigger post-traumatic symptoms (Smith et al., 1999; Cordova et al., 2017; Banik et al., 2019; Panzeri et al., 2023) such as intrusion, avoidance, and hyperarousal (Bates et al., 2023; Rossi et al., 2024a), as well as a broader pattern of psychological distress that includes anxiety, depression (Fischer and Wedel, 2012; Lo-Fo-Wong et al., 2016), and adjustment disorders. Furthermore, surgical interventions such as mastectomy or quadrantectomy can carry additional traumatic implications, affecting body image and the related psychological sphere (Maguire, 1985; Rossi et al., 2022, 2024a).

These traumatic responses can be attributed to multiple factors. Indeed, patients face a direct confrontation with mortality, experiencing fears regarding treatment outcomes and survival that exacerbate emotional distress (Abbey et al., 2015; Swartzman et al., 2017) – often intensified by fear of recurrence contributing to chronic anxiety and PTSD-related symptoms (Mehnert et al., 2009). Cancer also entails a profound loss of control over one’s body and fate, particularly in breast cancer where mastectomy physically alters the body and instills feelings of vulnerability and helplessness (Mehnert et al., 2009; Danhauer et al., 2013). Furthermore, uncertainty surrounding prognosis and treatment efficacy creates persistent trauma-related distress, with patients reporting intrusive thoughts and hyperarousal linked to the unpredictability of their condition (Andrykowski and Cordova, 1998; Mehnert and Koch, 2007). Finally, the invasiveness of medical procedures represents a continuous source of traumatic exposure throughout the treatment trajectory (Cordova et al., 2017).

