### Body image and femininity in breast cancer

1.3

The impact of mastectomy on body image represents a critical dimension of the psychological burden experienced by breast cancer patients (Türk et al., 2018). For many women, breasts symbolize femininity, sexuality, beauty, and motherhood, and their removal through mastectomy can result in profound disturbances to body image and self-concept (Fang et al., 2013; Koçan and Gürsoy, 2016). Research has documented that negative body image following mastectomy includes dissatisfaction with appearance, perceived loss of femininity and body integrity, reluctance to look at one’s body, feeling less sexually attractive, self-consciousness about appearance, and dissatisfaction with surgical scars (Koçan and Gürsoy, 2016; Latifee et al., 2025).

Studies have shown that mastectomy can be experienced as a sense of mutilation and diminished self-worth, threatening perceptions of femininity and potentially causing more psychological trauma than the cancer diagnosis itself (Fang et al., 2013; Türk et al., 2018). Body image distress is associated with additional complications including reduced quality of life, depression and anxiety symptoms, social isolation, and impairments in sexual functioning (Weingarden et al., 2022; Latifee et al., 2025). These psychological impacts may persist long after treatment completion, affecting social reintegration and intimate relationships, with some studies suggesting that adaptation may take up to 2 years following surgery (Izydorczyk et al., 2018).

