#### Randomization and blinding

2.2.5

The study employs a single-blind RCT design. Participant allocation to one of the three groups (TAU vs. TAU + psychoeducation vs. TAU+R-TEP) will follow rigorous procedures ensuring allocation concealment.

First, each participant will be assigned a unique identification code ensuring individual anonymity. Second, group allocation will be conducted through dedicated web-based software (Randomization.com) (Randomization, 2025) by two independent persons meeting the following requirements: (1) external to the project; (2) unaware of study objectives; (3) with no access to participant information; and (4) without mutual contact. If any condition is not met, these individuals will be replaced. This procedure ensures proper allocation concealment. Regarding blinding, participants are blinded to group assignment rationale, while treating clinicians are necessarily aware of intervention type given the nature of psychological treatments. Participants will be assigned to conditions within seven working days from baseline assessment.

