### Outcome measures

2.5

In accordance with study objectives, this research protocol assesses a comprehensive range of psychological outcomes relevant to breast cancer patients, including affective symptoms, trauma-related distress, body image, self-esteem, emotion regulation difficulties, perceived social support, and global psychological functioning.

An anamnestic form will collect sociodemographic variables (age, marital status, education, family composition, employment status, current intimate relationship information), immigration status, alcohol consumption, substance abuse, and notable life events (separation, bereavement, etc.). Additionally, beyond standard clinical interview, temporal changes will be monitored using validated Italian-language self-report instruments.

All assessments will be administered at baseline (T0), after surgical intervention (T1), after completion of the psychological intervention (T2), and at 3-month follow-up from the complention of the psychological intervention (T3) - to evaluate long-term changes.

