### Statistical analysis

2.6

Statistical data analyses will be performed using R software (R Core Team, 2017). Throughout data collection duration, *in itinere* statistical analyses will verify data quality and potential bias absence. Regarding missing data management, participants who discontinue the study (dropouts) will be excluded from analyses due to concerns about response validity. Similarly, assessment batteries with more than 10% missing items will be considered invalid and excluded. For remaining missing data within valid batteries, appropriate handling methods (e.g., multiple imputation, full information maximum likelihood) could be employed depending on missing data patterns and mechanisms.

Preliminary analyses will verify group homogeneity regarding relevant variables (age, comorbidity, social support, etc.) and possible intervening variable influence (covariates). If deemed appropriate and/or if significant heterogeneity is detected between groups, such variables will be included as covariates in the analysis models. Preliminary analyses will also verify psychometric instruments’ internal consistency (McDonald’s omega) (McDonald, 1999).

Both group-level aggregate analyses and individual change-focused evaluations will be employed. At group level, longitudinal changes will be examined using appropriate linear models for repeated measures data (e.g., linear mixed models or repeated measures ANOVA, or Bayesian approaches), depending on data characteristics such as distribution, missing data patterns, and sphericity assumptions (Howell, 2013; Darlington and Hayes, 2017; van den Bergh et al., 2023). Also, if appropriate, multilevel analysis – random slopes and/or random intercepts – may be implemented in the models (Hox et al., 2017; Heck and Thomas, 2020; Finch and Bolin, 2024). Model selection will be guided by standard diagnostic procedures. All models will test the interaction between time and intervention group – and where appropriate – controlling for individual variability and potential covariates identified in preliminary analyses.

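### Mastectomy and quadrantectomy patients are pooled, but surgery type is neither a named stratum nor a prespecified model term: a minor weakness with a cheap remedy

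*Protocol article*

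**What the plan says.** Section 2.2.2, criterion 4, reads "Have scheduled surgical intervention (mastectomy or quadrantectomy", so both operations enter one trial population. The expected mix is not given.

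The background mentions surgery in two ways. Section 1.1 names the operations together: "surgical interventions such as mastectomy or quadrantectomy can carry additional traumatic implications, affecting body image and the related psychological sphere". Section 1.3 deals with mastectomy only, opening with "The impact of mastectomy on body image represents a critical dimension of the psychological burden experienced by breast cancer patients" and later describing it as "potentially causing more psychological trauma than the cancer diagnosis itself".

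On allocation, section 2.2.5 says "group allocation will be conducted through dedicated web-based software (Randomization.com" and describes two independent outside persons and concealment. It names no stratification factor and no blocking. It places assignment within seven working days of baseline, which is before surgery. Section 2.4.2 places it after T1, which falls within a week after surgery.

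On covariates, section 2.6 will "verify group homogeneity regarding relevant variables (age, comorbidity, social support, etc", an open list that does not name surgery. A variable enters the models if that is thought appropriate or if the groups differ significantly. The tested term is group by time, and section 2.2.4 powers it over T0 to T3.

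**The concern.** Arms of about 34 are small enough for a two-category characteristic to split unevenly by chance. If patients who lose a breast follow a different course on distress or post-traumatic symptoms from those who keep it, an uneven split puts part of that difference into the treatment contrast of this one trial, and the variation due to surgery stays in the error term.

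Two features of the plan give this some weight. The tested interaction includes T0, which precedes surgery, so any surgery effect on change from T0 enters the group-by-time contrast when the arms are unbalanced. And the safeguard in section 2.6 relies on a baseline significance test or an unspecified judgement, made after the data are in. The information needed to do better is available: the planned operation is known at eligibility, and the operation performed is known if allocation follows surgery.

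**Working it through.** **The plan's own figure.** Section 2.2.4 gives f = 0.15, correlation 0.35, two-sided α = 0.05, power 0.80, 3 groups and 4 timepoints. For the within-between interaction, λ = f²·N·m/(1−ρ) = 0.0225 × 102 × 4 / 0.65 = 14.12, with df1 = 2 × 3 = 6 and df2 = 99 × 3 = 297. Power is 0.807. At N = 99 it is 0.793. The stated 102 (34 per arm) reproduces, and nothing below disputes it.

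**Chance imbalance.** Assumptions: simple randomisation, 34 per arm, mastectomy share p of 20–40% (the documents give none). The standard deviation of the difference in share between two arms is √(2p(1−p)/34). The other columns come from 400,000 simulated trials with three binomial arms.

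| p | SD of difference | R-TEP vs TAU gap ≥ 20 points | Any pair gap ≥ 20 points |
|---|---|---|---|
| 0.2 | 0.097 | 5% | 12% |
| 0.3 | 0.111 | 8% | 20% |
| 0.4 | 0.119 | 11% | 24% |

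At about 41 per arm (122/3, all recruited) the two probabilities fall to 2–5% and 5–13%.

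**Would the section 2.6 test find it?** Among simulated trials in which some pair differs by at least 20 points, a three-arm chi-square test at 0.05 is significant in only 22–44%, the higher figure belonging to p = 0.2. For example, 7/34, 10/34 and 14/34 mastectomies is a 21-point spread with chi-square 3.43 on 2 df, p = 0.18.

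**Effect on the outcome contrast.** The shift is the gap times the surgery effect. For a 20-point gap and an assumed surgery effect of 0.2–0.8 SD it is 0.20 × 0.2 = 0.04 SD to 0.20 × 0.8 = 0.16 SD. The standard error of a pairwise difference at one timepoint is √(2/34) = 0.24 SD. For a difference in change between two timepoints, with correlation 0.35, it is √(2 × 0.65) × √(2/34) = 1.14 × 0.243 = 0.28 SD. The shift is below one standard error in both cases.

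**Which model term helps.** The group-by-time contrast is built from within-patient differences. A term for surgery that is constant over time cancels from those differences. A fit to simulated complete data (34 per arm, four timepoints) confirmed this: adding a surgery main effect left the group-by-time estimates and standard errors identical, while adding surgery by time changed them. A main effect would therefore not protect the planned test.

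**Precision.** If surgery-related change explained 1–10% of the error variance, replacing f by f/√(1−R²) raises power from 0.807 to about 0.81–0.85, ignoring the few degrees of freedom used.

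**The case against.** Several stronger readings are tempting, and the document does not support them.

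- *The protocol itself declares the two operations differently traumatic.* It does not. Section 1.1 names them together, and the comparison in section 1.3 is between mastectomy and the cancer diagnosis. That surgery type is prognostic for PDI-R or PTSQ is a plausible inference, not a statement in the protocol. The link is closest for body image, which is a secondary outcome analysed as exploratory.
- *Allocation is stated to be unstratified.* Section 2.2.5 is silent on lists, blocks and strata. This is a condensed article, and silence is weaker evidence than a statement of none.
- *Surgery type will not be recorded.* The statement "An anamnestic form will collect sociodemographic variables" describes one form. Comorbidity is a named covariate and is not listed there either, so other data sources must exist.
- *The comparison is biased.* Randomisation without strata is unbiased, and type I error holds.

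Two further objections have partial force. First, the covariate list is open, so surgery type can be added even without a significant imbalance. That is true, but the discretion is unspecified, and the significance route misses most gaps of 20 points or more. Second, under section 2.4.2, T1 comes after surgery and before allocation, so surgery-related differences already present at T1 are observed before treatment. That limits the harm if the analysis uses T1 as its reference. The powered test, however, spans T0 to T3, and no T1-adjusted model is fixed. Even with T1 adjustment, a correlation of 0.35 means about 12% shared variance (0.35² = 0.1225).

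**Conclusion.** The point holds as a minor, cheap improvement, not as an error. Two operations are pooled, no stratum is named, and adjustment for surgery type depends on a later judgement or a weak test. The chance of a 20-point imbalance is modest for the main comparison and somewhat larger for any pair of arms. When it occurs, the expected distortion is smaller than one standard error. These sizes rest on a mastectomy share and a surgery effect that the protocol does not give, and on simple randomisation. Blocking or stratification set out in a fuller protocol would reduce them.

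**What to change.** 1. Reconcile sections 2.2.5 and 2.4.2 on when allocation occurs. Both can hold only if surgery and T1 fall within seven working days of baseline.
2. In section 2.2.5, state that allocation is 1:1:1 in permuted blocks, stratified by surgery type: the operation performed if allocation follows surgery, the scheduled operation otherwise. If the full protocol already stratifies, say so.
3. In section 2.6, prespecify for PDI-R and PTSQ a surgery term together with its interaction with time, or surgery as a covariate in a model of T2 and T3 adjusted for T1. Include it whatever the baseline comparison shows.
4. Confirm that surgery type is captured in the study data.

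The cost is two allocation lists instead of one, and a few degrees of freedom: 3 of 297 within-patient and 1 of 99 between-patient for the surgery-by-time model. N = 102 is unchanged. If recruitment has begun, the model term alone can still be added.

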#### Exclusion criteria

2.2.3

Participants will be excluded if they: (1) present with metastatic disease; (2) have cognitive impairment compromising understanding of informed consent and/or assessment instruments; (3) have history of severe psychiatric diagnosis with current psychotropic medication use; (4) presence of pre-existing PTSD unrelated to oncological illness; (5) clinically significant dissociative symptoms as indicated by (A) a clinical psychological examination and/or (B) a score higher than 30 on the Dissociative Experiences Scale-II (DES-II; Carlson and Putnam, 1993) – as severe dissociation may interfere with standard EMDR protocols and require adapted treatment approaches (van der Hart et al., 2006; ISSTD, 2011; Leeds et al., 2023).

#### Sample size calculation

2.2.4

An *a priori* power analysis was conducted to calculate the minimum sample size required for this study, following established statistical procedures (Perugini et al., 2018; Taccini et al., 2022). The G*Power software (V.3.1.9.2) (Faul et al., 2007, 2009) was utilized to determine the required sample size for repeated measures analysis of variance (ANOVA) with within-between interaction. The research protocol involves four assessment timepoints, with treatment condition as between-group variable (TAU vs. TAU + psychoeducation vs. TAU+R-TEP) and time as within-subject variable (T0, T1, T2, and T3; see dedicated section).

Given the absence of prior studies implementing this specific intervention protocol, conservative a priori parameters were adopted. These were informed by examining previous studies utilizing similar interventions (though not identical), comparable target samples, and similar constructs. The effect size *f* was set to 0.15 (small-to-medium effect size) and the correlation among repeated measures was set to 0.35. Type I error rate probability (*α*) was set to 0.05 (two-sided), and power (1-*β*) was set at 0.80 (Cohen, 1988; Eid et al., 2017; Perugini et al., 2018).

G*Power analysis indicated 80% probability of correctly rejecting the null hypothesis of no significant group-by-time interaction effect with an overall sample of 102 participants (approximately 34 subjects per group). Based on average patient flow to the unit, to account for an anticipated attrition rate of approximately 20%, the study aims to recruit at least 122 patients, ensuring adequate statistical power for the planned analyses.

The three groups will each comprise a minimum of 34 patients: (A) Control group (G1): Patients receiving standard routine psychological support (TAU); (B) Active control group (G2): Patients receiving weekly psychoeducation session plus TAU; (C) Experimental group (G3): Patients receiving EMDR R-TEP intervention plus TAU.

This sample size is highly feasible considering service patient flow while simultaneously permitting statistical analyses generating reliable estimates.

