### Study aims and hypotheses

1.8

The present research project aims to implement, refine, and evaluate the efficacy of a psychological intervention supporting women affected by breast cancer who have undergone mastectomy or quadrantectomy. To achieve this objective, in addition to the standard psychological support intervention (treatment as usual; TAU), innovative integrated interventions will be applied, including psychoeducational interventions and interventions utilizing the potential of the EMDR R-TEP protocol.

Through a solid experimental methodology implemented as a randomized controlled trial (RCT), the project aims to identify the most effective intervention modalities for providing integrated psychological support to women with breast cancer. In a broader perspective, the study aims to provide a significant contribution not only to the scientific literature in the field but also to clinical practice, contributing to the optimization of clinical practices in oncology.

Specifically, the primary objective of the research is threefold:

To evaluate over time whether the EMDR R-TEP protocol produces clinically and statistically significant improvements in psychological variables of interest, including anxiety, depression, distress, hopelessness, traumatic impact of cancer diagnosis, psychological well-being, and global psychological symptomatology;To assess the relative efficacy of the EMDR R-TEP protocol by analyzing differences in psychological variable improvements compared with the group receiving psychoeducational intervention and a control group receiving routine standard psychological support treatment (TAU);To evaluate on which psychological variables the EMDR R-TEP protocol is capable of producing the greatest changes in terms of well-being, post-traumatic symptomatology, and stability over time.

It is hypothesized that the EMDR R-TEP protocol, combined with standard psychological support, will demonstrate superior efficacy in significantly reducing levels of distress, post-traumatic symptoms, and other psychological symptomatology (e.g., anxiety and depressive symptoms), compared to both TAU alone and TAU in addition to psychoeducation. The relative efficacy over time of the different treatments will be assessed through retest of the questionnaires identified in the assessment battery.

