
#### Strengths

3.3.2

The present study presents several methodological strengths. First, the randomized controlled trial design with active comparison groups represents gold-standard evidence generation, minimizing bias and enhancing confidence in findings. Second, multi-dimensional evaluation across validated instruments provides comprehensive assessment and detailed understanding of intervention effects and mechanisms. Third, sample size calculations ensure adequate statistical power to detect clinically meaningful effects, reducing false negative risk. Fourth, the manualized R-TEP protocol enhances internal validity, treatment fidelity, and future replicability through standardized intervention delivery. Fifth, the intervention addresses a genuine unmet clinical need with feasible implementation potential in real-world oncological settings, ensuring clinical relevance. Finally, early post-surgical implementation capitalizes on prevention opportunities rather than waiting for chronic symptom development, allowing for timely intervention.

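### The sample size of 102 is correct for one omnibus interaction test, but the assumed effect is about 0.64–0.85 SD between R-TEP and TAU, so the general claims of adequate power are overstated

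*Protocol article*

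**What the plan says.** Section 2.2.4 (Sample size calculation) bases the trial on a G*Power calculation for "repeated measures analysis of variance (ANOVA) with within-between interaction", with three groups, four visits, alpha 0.05 and power 0.80. It says that "conservative a priori parameters were adopted" and that f "was set to 0.15 (small-to-medium effect size) and the correlation among repeated measures was set to 0.35". The result is an "80% probability of correctly rejecting the null hypothesis of no significant group-by-time interaction effect with an overall sample of 102 participants", about 34 per group. The section then describes the recruitment target as "ensuring adequate statistical power for the planned analyses".

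Section 3.3.2 (Strengths) goes further: "sample size calculations ensure adequate statistical power to detect clinically meaningful effects".

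The main hypothesis in section 1.8 is pairwise. R-TEP is to be superior "compared to both TAU alone and TAU in addition to psychoeducation". Section 2.6 lists the three pairwise contrasts as post-hoc comparisons. Section 3.1 expects psychoeducation to do better than TAU and R-TEP to do better than both, with the R-TEP advantage clearest at T3. Section 2.4.2 places randomisation and the intervention after T1.

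**The concern.** An f of 0.15 for a within-between interaction does not translate directly into a familiar between-arm difference. It is averaged over all group-by-visit cells, and here half of the visits precede treatment. A reader told that the effect is small-to-medium and conservative will picture a modest difference between arms and will assume that the trial can detect it.

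The protocol never converts f into a difference between arms, and it states no clinically meaningful difference for either primary outcome. Section 3.3.2 therefore has nothing to rest on when it claims power for such effects. The calculation also does not address R-TEP versus psychoeducation, which half of the hypothesis depends on. If that contrast is not significant, the published power statements invite the reader to treat it as informative when it may be merely imprecise.

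**Working it through.** **Inputs.** From section 2.2.4: f = 0.15, correlation ρ = 0.35, k = 3 groups, m = 4 visits, alpha 0.05, N = 102 (34 per group). From section 2.4.2 and the abstract: T0 and T1 both precede the intervention. Assumed here, because the article gives no means: the patterns of arm means at T2 and T3. All differences are in single-visit SD units.

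**1. Reproduce the stated N.** G*Power's default for this test uses λ = f²·N·m/(1 − ρ), df1 = (k − 1)(m − 1) = 6 and df2 = (N − k)(m − 1).
- At N = 102: λ = 0.0225 × 102 × 4 / 0.65 = 14.12, df = 6 and 297, power 80.7%.
- The smallest N reaching 80% is 101 (80.2%); 102 is the next multiple of three.
- Under the two other definitions of f that the software offers, N would be about 205–207.

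The stated N is therefore correct. It also fixes what f means here: the SD of the interaction effects over the 12 group-by-visit cells, divided by the single-visit SD.

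**2. Convert f to a difference d between R-TEP and TAU.** If the arms share a time profile, f = d·√(Vg·Vt). Vg is the variance (divisor 3) of the arm positions, with TAU = 0 and R-TEP = 1. Vt is the variance (divisor 4) of the time profile, with zeros at T0 and T1.

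| Pattern | Vg | Vt | f per unit d | d at f = 0.15 |
|---|---|---|---|---|
| Psychoeducation = TAU, T2 = T3 | 2/9 | 1/4 | 0.236 | 0.64 |
| Psychoeducation midway, T2 = T3 | 1/6 | 1/4 | 0.204 | 0.735 |
| Psychoeducation midway, T3 only | 1/6 | 3/16 | 0.177 | 0.85 |
| Psychoeducation midway, T2 half of T3 | 1/6 | 11/64 | 0.169 | 0.89 |

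The arms need not share a profile. In an extreme case psychoeducation equals R-TEP at T2 and falls back to TAU at T3. The squared interaction effects then sum to (6/9 + 6/9) − 4 × (2/16) = 0.833 d², so f = d·√(0.833/12) = 0.264 d and d = 0.57.

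**3. Omnibus power at N = 102 if the true effect is smaller** (psychoeducation midway, T2 = T3).
- d = 0.3: f = 0.061, power 16%.
- d = 0.4: f = 0.082, power 28%.
- d = 0.5: f = 0.102, power 43%.

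With psychoeducation equal to TAU the corresponding figures are 21%, 37% and 56%.

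**4. R-TEP versus psychoeducation under the plan's own f.** With psychoeducation midway and a lasting effect, the difference is 0.735/2 = 0.37 SD. Pairwise power uses a noncentral t with 66 df and noncentrality (d/s)·√(34/2), before any multiplicity correction. Here s is the residual SD implied by ρ = 0.35.
- t test at one visit: s = 1, noncentrality 1.51, power 32%.
- ANCOVA at T3, adjusting for the mean of T0 and T1: s = √(1 − 0.35²/0.675) = 0.905, power 38%.
- Mean of T2 and T3, with the same adjustment: s = √(0.675 − 0.35²/0.675) = 0.703, power about 57%.

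With the same three methods, R-TEP versus TAU at 0.735 SD has 85%, 91% and 99% power. The weak point is the contrast with psychoeducation.

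**The case against.** **The calculation and the label are nominally right.** This stands. N = 102 reproduces, and 0.15 lies between the conventional f benchmarks of 0.10 and 0.25. A reader might infer an arithmetic error; there is none. The sentence giving the 80% figure also names the interaction test correctly. The overstatement lies in the broader sentences.

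**Part of the parameter set is conservative.** This also stands. At f = 0.15, a correlation of 0.5 would need 78 patients and 0.6 would need 63, so choosing 0.35 raises N. At ρ = 0.6 the omnibus power for 0.3–0.4 SD (psychoeducation midway) would be 25–45%, which is better but still low. The word fits ρ and does not fit f.

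**A reader might infer that the trial can detect only large differences.** The documents do not support that. Section 2.6 allows mixed models and covariates. A baseline-adjusted R-TEP versus TAU contrast averaged over T2 and T3 has 82% power at 0.5 SD. The article does not commit to that contrast, but neither does it rule it out.

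**A reader might also lower the power by splitting alpha over the two primary outcomes.** Section 2.6 names a False Discovery Rate procedure, to be used if necessary, so a Bonferroni-style reduction is not what is planned.

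**The SD figures rest on assumed means.** They do. Section 3.1 orders the arms but gives no distances. If psychoeducation were equal to TAU, R-TEP versus psychoeducation would be 0.64 SD, with about 74% power at one visit and up to 96% averaged and adjusted. That is not the ordering that section 3.1 expects.

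**Conclusion.** The concern holds as an overstated power claim, not as a miscalculation. The design has 80.7% power for one omnibus interaction test at an effect equal to about 0.64–0.85 SD between R-TEP and TAU. The value is somewhat higher if the effect grows from T2 to T3, and about 0.57 SD in the extreme fading pattern. All of these are medium-to-large, against a comparator that itself receives individual support twice weekly.

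The statements that power is adequate for the planned analyses and for clinically meaningful effects are not supported. With psychoeducation midway, R-TEP versus psychoeducation has 32–57% power depending on the method, and the omnibus test has 16–28% if R-TEP versus TAU is 0.3–0.4 SD. These figures assume 34 analysed per arm, ρ = 0.35, equal arms at T0 and T1, and the stated patterns of means. The 0.3–0.4 SD scenario is illustrative, because the article gives no SD or minimal important difference for either primary outcome.

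**What to change.** In section 2.2.4:
- State beside f = 0.15 the implied R-TEP minus TAU differences and the patterns behind them (0.64, 0.735 and 0.85 SD).
- Apply the word conservative to the correlation only.
- Limit the closing statement on adequate power to the omnibus group-by-time interaction.
- Report the power of R-TEP versus TAU and of R-TEP versus psychoeducation at 34 per arm, under stated patterns and for a named method of analysis.

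Qualify the corresponding sentence in section 3.3.2 in the same way. Add that a non-significant R-TEP versus psychoeducation contrast is inconclusive and will be interpreted from its confidence interval.

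The cost is a less favourable stated figure. No patients are added and the design does not change.
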